#### Questionnaire P2 – by the patient – 3 months postoperative

Collected data: complications, recurrence, use of analgesics at that time, VDS pain score at rest, pain score while exercising and VDS cosmetic score.

#### Questionnaire D3 – by the doctor – 1 year postoperative

Collected data: recurrence, use of analgesics at that time, VDS pain score at rest, pain score while exercising and VDS cosmetic score.

#### Questionnaire P3 – by the patient – 2 years postoperative

Collected data: recurrence, use of analgesics at that time, VDS pain score at rest, pain score while exercising and VDS cosmetic score.

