## Background

The evidence that umbilical and epigastric hernias must be repaired using a mesh, in analogy with other hernias, is accumulating [1-7]. The use of a mesh in large hernias reduces the risk of recurrence from approximately 15-40% to 1-10% [1,4-6,8-10]. However, less research has been performed if this also applies for small hernias. To date, most small hernias are still closed with primary sutures, because of the sometimes-difficult pre-peritoneal plane in which the mesh should be placed. Therefore, the results of the Hernia Umbilicalis Mesh versus Primair suture (HUMP) trial that focuses on hernias smaller than 2 centimetres will have great added value for umbilical hernias in particular [11]. Other retrospective studies suggest that for the reoperation rate due to recurrence mesh is superior in umbilical and epigastric hernias [7]. In contrast to the HUMP trial, which places the mesh in this pre-peritoneal plane, a mesh can also be placed intraperitoneally. Advantages of intraperitoneal mesh placement can be shorter operation time. Intraperitoneal mesh placement can also be done by a laparoscopic approach [12-14]. Although in the laparoscopic mesh placement, several new fascia openings in the abdominal wall are created. The search for alternative techniques without these additional fascia defects may have played an important role in the development of these so-called patches. Patches are small devices, which can be inserted by open surgery and placed underneath the peritoneum [15-17].

In theory, such patches are particularly suitable for small hernias because of the lesser dissection necessary. It is still unclear whether this simpler procedure is also associated with at least an equal risk of recurrence and complications compared to conventional mesh placement. The ease of a surgical procedure is not a clear clinically relevant parameter, but it does often play a significant role in the surgeon’s choices. Not only are there implications for approximately 4100 umbilical and 2400 epigastric operations in the Netherlands per year [18], but also for a frequently occurring other abdominal wall hernia, the small incisional hernia.

The MORPHEUS trial is designed to clarify which treatment for primary umbilical and epigastric hernias is superior in terms of complications, costs and recurrence.

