### Follow-up and flow chart protocol

The surgeon must fill in a questionnaire (D1) immediately after the operation. The patients are advised to take 1 gram of paracetamol 3 times a day for the first 2 weeks, and to begin mobilizing immediately according to their capacity. Follow-up at the outpatient clinic takes place after 1 and 12 months, with the practitioner filling in the questionnaires (D2 and D3). The patients are asked to fill in a questionnaire 3 and 24 months after the operation (P2 and P3). These questionnaires will be sent to the patients by postal service or e-mail. Non-responders were contacted up to three times by means of a telephone questionnaire. Figure 1 shows the studies flow-chart.

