### Publication

The plan is to create three publications. The primary endpoint with short-term results will be processed in one report. This will be one month post-operatively. The the long-term results will be processed in two another report. One report with one-year results and one with two-year result. In the two-year results report, recurrence will be added as secondary outcome measure. Co-investigators with a contribution of at least 10% of the number of patients required will be asked for co-authorship.

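### Recurrence at 24 months is patient-reported with no stated confirmation, and the clinic-recorded 12-month result is not named for any report

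*Protocol article*

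**What the plan says.** The Follow-up and flow chart section of the Protocol article fixes who sees the patient and when. "Follow-up at the outpatient clinic takes place after 1 and 12 months, with the practitioner filling in the questionnaires (D2 and D3"). The other two contacts are remote: "The patients are asked to fill in a questionnaire 3 and 24 months after the operation (P2 and P3"). On delivery and chasing it says "These questionnaires will be sent to the patients by postal service or e-mail" and "Non-responders were contacted up to three times by means of a telephone questionnaire".

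The Data outcome section lists recurrence on three forms: P2 (patient, 3 months), D3 (doctor, 12 months) and P3 (patient, 24 months). For P3 the entry reads "Collected data: recurrence, use of analgesics at that time, VDS pain score at rest, pain score while exercising and VDS cosmetic score". D3 is the only doctor-completed form that lists recurrence.

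The Publication section plans a short-term report, a one-year report and a two-year report, and places recurrence in the last: "In the two-year results report, recurrence will be added as secondary outcome measure". The Post-operative paragraph of the statistical section lists signs of recurrence at 1, 3, 12 and 24 months without saying who recorded them.

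The Blinding section adds two facts. Patients learn their device through P3, and the physician seen during follow-up is not blinded.

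The only recurrence rates are in the Background: "The use of a mesh in large hernias reduces the risk of recurrence from approximately 15-40% to 1-10" per cent. The next sentence limits them: "However, less research has been performed if this also applies for small hernias".

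**The concern.** The Background says the trial should show which treatment is superior on complications, costs and recurrence. The final recurrence result depends on patients judging for themselves, two years on, whether the hernia has returned. Some will report one that an examination would not confirm, and some will not notice a real one.

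When the event is uncommon, a modest false-positive rate adds many cases to both arms. If the error is equal in the two arms, the risk ratio moves towards 1 and power drops, so a worse device can look equivalent. If the error differs between the arms, the comparison is biased, and the direction cannot be known in advance. The doctor's 12-month record is less exposed to this, but no report is named for it.

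**Working it through.** **Inputs from the document.** 346 patients randomised, 10% loss allowed for, significance level 5%. With equal arms, 346 / 2 × 0.90 = 155.7, or 156 per arm and 312 in total. The plan gives no sample size or power for recurrence, so there is no figure of its own to reproduce.

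**Assumptions.** The document does not give the accuracy of patient report. I take sensitivity (Se) 0.90 and specificity (Sp) 0.95, with Sp 0.98 and 0.90 as the range. True rates of 1%, 5% and 10% span the Background's range for mesh repair. That range is stated for large hernias, while this trial admits orifices up to 3 cm, so using it here is an extrapolation.

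**Reported rates.** Reported = p × Se + (1 − p) × (1 − Sp). At Se 0.90 and Sp 0.95:
- p = 1%: 0.009 + 0.0495 = 5.85%; share of reports that are real 0.009 / 0.0585 = 15%
- p = 5%: 0.045 + 0.0475 = 9.25%; share real 0.045 / 0.0925 = 49%
- p = 10%: 0.090 + 0.045 = 13.5%; share real 0.090 / 0.135 = 67%

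For 5% versus 10%, the difference shrinks from 5.0 to 4.25 points and the risk ratio from 2.0 to 1.46. For 1% versus 10%, the risk ratio shrinks from 10 to 2.31.

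**Power.** Exact power of the two-sided 5% chi-square test, 156 per arm, Se 0.90. The last column removes all false positives, so the rates are p × 0.90.

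| True rates | Perfect ascertainment | Sp 0.98 | Sp 0.95 | Sp 0.90 | Reported cases confirmed |
|---|---|---|---|---|---|
| 5% vs 10% | 38% | 28% | 22% | 16% | 35% |
| 1% vs 10% | 97% | 82% | 64% | 44% | 96% |
| 1% vs 5% | 56% | 31% | 20% | 14% | 50% |

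A normal approximation with 155 per arm agrees closely: 39% to 22% for the first row and 94% to 63% for the second, at Sp 0.95.

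**How many false reports equal the true cases?** With 312 patients and Se 1, the true cases number 312 × p: about 3 at 1%, 6 at 2%, 16 at 5% and 31 at 10%. False reports reach those counts when Sp falls to 1 − p / (1 − p): 99.0%, 98.0%, 94.7% and 88.9%.

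**Unequal error.** Suppose both arms truly have 5% recurrence and Se is 0.90, but Sp is 0.95 in one arm and 0.98 in the other. The reported rates are 9.25% and 0.045 + 0.95 × 0.02 = 6.4%. That is a difference of 2.85 points where none exists.

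**Cost of checking.** Expected reports for 5% versus 10% at Sp 0.95: 156 × (0.0925 + 0.135) = 35.5, so about 35. Over all the scenarios in the table the number runs from about 15 to about 50.

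**The case against.** Several objections have force.

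- **Rarity.** A reader might infer that a few false reports would swamp the true cases anywhere in the 1-10% range. They would not. Three to six false reports match the true cases only near 1-2% recurrence. In the 5% versus 10% scenario at Sp 0.95, reported true cases are 156 × 0.90 × 0.15 = 21 and false reports are 156 × 0.05 × 1.85 = 14.
- **Clinic record.** A reader might infer that recurrence is never examined. D3 records it in clinic at 12 months, so first-year recurrences have a doctor's record. If the two-year analysis draws on D3 for them, fewer true cases depend on P3 alone and the power loss would differ from the table.
- **Pooling and withholding.** A reader might infer that patient and clinic reports are merged, or that the D3 result is kept out of the one-year report. Neither is stated. The Post-operative list is by time point, and the Publication section is silent on 12-month recurrence.
- **Power is low anyway.** Recurrence is secondary and was not used to size the trial. At 5% versus 10% power is only 38% even with perfect ascertainment. This stands for that scenario, but not for 1% versus 10%, where self-report costs a well-powered comparison a third of its power.
- **Condensed article.** The wording of P3, the definition of recurrence and the handling of a positive answer may be in the full protocol. That is possible, and their absence is not the point. Who completes P3, when clinic visits take place and which report carries recurrence are all fixed here.
- **Unblinded confirmation.** The surgeon who would confirm a report knows the device, and only positive reports would be checked. This stands, and it limits what confirmation can achieve.

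**Conclusion.** The point holds as a limitation of one secondary outcome that deserves correction. The 24-month recurrence status is patient-reported with no stated confirmation, and recurrence is named only for the two-year report although a doctor records it at 12 months. On the assumed accuracy, power falls from 38% to 22% (5% versus 10%) or from 97% to 64% (1% versus 10%). These figures rest on assumed sensitivity and specificity, on equal error in both arms, on a result taken wholly from the questionnaire, and on recurrence rates borrowed from large hernias.

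It would be tempting to say that the error can only pull the arms together. The document does not support that, because P3 itself discloses the device. Whether patients read the disclosure before answering is not stated, so the error may be equal or unequal, and the bias may run either way.

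**What to change.** 1. Name clinic-assessed 12-month recurrence (D3) as an outcome of the one-year report. The data are already collected, so this costs only wording.
2. State that doctor-recorded and patient-reported recurrence are analysed and presented separately.
3. For a recurrence reported on P2 or P3, seek confirmation by an outpatient check with the patient's own surgeon or by a documented re-repair.
4. Present confirmed recurrences and all reported recurrences side by side, by arm, with the number not examined.
5. Collect the P3 recurrence answer before the device is disclosed, for example by sending the disclosure after the form is returned.

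The cost is protocol wording, a change in the P3 mailing and about 35 outpatient checks among 312 patients on the main assumptions. The Post-trial care section already makes the hospital surgeon responsible for long-term care. Three downsides remain: recurrences the patient does not notice are still missed, the confirming surgeon is not blinded, and patients who do not attend stay unconfirmed. The last two are the reason to show both counts and not let the confirmed count replace the reported one.

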### Definitions

A complication is defined as an undesired development that requires treatment, related to the operation site, occurring within 3 months postoperative. Treatment could also been initiated by the general practitioner, or other than that by the hospital surgeon. Complications are defined as following:

Extending operation time due to bleeding or other injury during the procedure

Prescribed medication treatment such as antibiotics and pain killers other than paracetamol after discharge

Re-operation such as evacuation of a haematoma, drainage of an abscess, exploration related to pain or intra-abdominal problems, or early recurrence

Wound care which requires more than once a day irrigation of the wound

Hospitalisation longer than scheduled or re-admission

The costs will be calculated post-hoc on the basis of the number of visits to the outpatient clinic, operation duration, costs of prosthesis and complication-related costs up to 2 years after the operation.

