### Objectives/Endpoints

The primary objective of the MORPHEUS trial is to evaluate whether a ventral patch is associated with fewer complications than in conventional mesh placement for epigastric and umbilical repair. A complication is defined as an undesired development that requires treatment. Complications will be recorded up to three months after the initial procedure and pain up to 24 months post-operative. Secondary endpoints are differences in recurrence, cosmetic score, operation duration and costs.

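### Costs run to 2 years but complications end at 3 months, so repair of a later recurrence falls under no named cost component

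*Protocol article*

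**What the plan says.** All references are to the Protocol article.

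- **Status of costs.** Objectives/Endpoints: "Secondary endpoints are differences in recurrence, cosmetic score, operation duration and costs". The Background adds that the trial should show which treatment is superior in complications, costs and recurrence.
- **Cost components.** The last paragraph of Definitions: "The costs will be calculated post-hoc on the basis of the number of visits to the outpatient clinic, operation duration, costs of prosthesis", followed by "complication-related costs up to 2 years after the operation". That makes four: outpatient visits, operation duration, prosthesis and complication-related costs.
- **What a complication is.** Definitions: "A complication is defined as an undesired development that requires treatment, related to the operation site, occurring within 3 months postoperative". Objectives/Endpoints uses the same limit for recording: "Complications will be recorded up to three months after the initial procedure".
- **Where recurrence enters that definition.** Only in the re-operation item, whose list ends "exploration related to pain or intra-abdominal problems, or early recurrence".
- **What the forms collect.** Operation duration is on D1, completed straight after the index operation. Complications are on D2 (1 month) and P2 (3 months). Recurrence is on P2, D3 (12 months) and P3 (24 months). D3 and P3 list neither complications nor re-operations.

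**The concern.** The cost endpoint has a 2-year horizon, but the component that would carry the cost of further surgery depends on a term that the same section closes at 3 months. A recurrence found at, say, 14 months and then repaired is not a complication under that definition, and its repair is not named anywhere else in the cost sentence.

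This matters because recurrence is an open question of the trial. The Background says it is still unclear whether the simpler patch procedure carries at least an equal recurrence risk. If one device recurs more after 3 months, the plan as worded leaves out a cost that falls mainly on that device. The bias has one direction: it makes the device with more late recurrences look cheaper than it is.

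**Working it through.** The plan gives no unit cost, cost total or cost difference, so there is no figure to reproduce. The check compares the text first and then sizes the gap.

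**Step 1. Test a repair at 14 months against each component.**

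| Component | Does it cover the repair? |
|---|---|
| Outpatient visits | Only the clinic visits the recurrence causes |
| Operation duration | No; it is collected on D1 for the index operation |
| Prosthesis | Not named for a second repair; no later form records a second device |
| Complication-related costs up to 2 years | Not under the definition, which requires an event "related to the operation site, occurring within 3 months postoperative" |

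**Step 2. Check whether the listed forms could supply the data anyway.** D3 and P3 would show that a recurrence exists, but not whether or when it was repaired. Hospital records might show this, but the article does not say they will be used.

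**Step 3. Size of the omission.** Let C be the cost of one repair, and let r1 and r2 be the proportions in each arm with a repaired recurrence after 3 months. The cost difference hidden per patient is

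H = (r1 − r2) × C.

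Inputs: the Background gives 1-10% recurrence with mesh in large hernias, and the sample-size section gives 346 randomised. Assumptions: allocation is 1:1, so 346 / 2 = 173 per arm; every recurrence arises after 3 months; every recurrence is repaired.

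| Late repair, lower v higher arm | H per patient | Unpriced excess repairs per 173-patient arm |
|---|---|---|
| Equal rates | 0 | 0 |
| 1% v 5% | (0.05 − 0.01) C = 0.04 C | 0.04 × 173 = 6.92 |
| 5% v 10% | (0.10 − 0.05) C = 0.05 C | 0.05 × 173 = 8.65 |
| 1% v 10% | (0.10 − 0.01) C = 0.09 C | 0.09 × 173 = 15.57 |

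The last row sets the two ends of the quoted range against each other. It is an outer bound for illustration, not an expected value.

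**Step 4. Boundary between components.** One listed complication is "Extending operation time due to bleeding or other injury during the procedure". The same minutes are also part of operation duration, and the text does not say under which heading they are priced. If a share c of the cost of a complication were priced under two headings, the planning rates of 20% and 10% would add (0.20 − 0.10) × c = 0.10 c complication costs per patient against conventional mesh: 0 at c = 0, 0.05 at c = 0.5 and 0.10 at c = 1. The document does not give c, and c = 0 is compatible with it.

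**The case against.** The strongest reply is that the 2-year phrase was meant to bring late recurrence surgery in. Definitions already treats re-operation for early recurrence as a complication, and the Post-operative statistics section attaches the 1, 3, 12 and 24-month time points to a list that includes complications. That may be the intention. It would, however, contradict the 3-month limit stated in two sections, and D3 and P3 list no item to support it. The other charitable reading, later costs of early complications, still leaves late repair out. Either way the horizon and the definition have to be reconciled. What stands is that this is a mismatch and not an explicit exclusion.

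It is also fair to say that the effect may be small or nil. The 1-10% range is for large hernias, whereas this trial takes orifices up to 3 cm. Some recurrences will be early and already costed, and not all will be repaired. Recurrence is reported as its own endpoint, so a difference would be visible beside the cost result. The primary endpoint is untouched.

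Two stronger readings are tempting, and the document does not support them:

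- A reader might infer that theatre time and clinic visits are counted twice. The cost sentence lists inputs; it gives no unit prices and no summing rule, so overlap is possible but not stated. Such an overlap would weigh against the arm with more complications and could not by itself favour the device that recurs more.
- A reader might infer from the word post-hoc that the cost endpoint is not prespecified. The same sentence fixes its components and horizon in advance, and costs are a declared endpoint. The word plausibly means calculated after data collection.

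Detailed costing rules are commonly left to a fuller document. This point is different: the article states a list of components, and that list does not fit its own definition and horizon.

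**Conclusion.** The point holds as a mismatch between a 2-year cost horizon and a 3-month complication definition. Followed literally, the plan counts nothing for a repair after 3 months beyond the clinic visits it causes, so any between-arm difference in late repair biases the cost comparison towards the device that recurs more.

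The size is (difference in late-repair rates) × (cost of one repair). It ranges from 0 to at most about 0.09 repair costs per patient under the step 3 assumptions. No figure in the document narrows that range for small hernias, and the direction cannot be assigned to either device in advance. The consequence is limited to a secondary endpoint, but the error lies in a stated rule and is easy to correct.

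**What to change.** 1. In the cost paragraph of Definitions, add re-operation for recurrence up to 24 months as a named cost component, separate from complication-related costs. The 3-month definition used for the primary endpoint can then stay as it is.
2. On D3 and P3, which already ask about recurrence, add an item: repaired yes/no, and date.
3. Add one sentence stating that each resource is priced once, so that extended operation time is not priced under both operation duration and complication-related costs.

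The cost is a change of wording, one extra item on two existing forms and slightly more data entry. No change to sample size, visits or the primary analysis is needed, and this point gives no reason to extend costing to every general-practitioner contact or bed-day.

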### Data collection methods

Completed informed consent forms remain at a central location of the participating hospital. When participating and signing, the patient receives a copy and the original stays at the hospital.

Questionnaires P1 and P2 with return envelope are given to the patient when he or she visits the outpatient clinic. P3 (2 years postoperative) is sent from the coordinating research hospital.

Questionnaires for surgeons D1-3 are preferably entered in an Excel/Access database on a hard disk accessible in the hospital. This can also be a paper version if so desired.

### Data management

Completed informed consent forms must be faxed/scanned/e-mailed to the coordinating research hospital. The questionnaires use codes consisting of the first initial and the first 2 letters of the last name followed by the serial number of the participating hospital; this to secure anonymity.

Informed consent forms and questionnaires remain in one place at the participating hospital. A password is used for the input program for surgeons.

